**Methods:**

The NAUTILUS trial is a prospective multicenter randomized controlled trial involving clinical stage T1–2 and N0 breast cancer patients receiving breast-conserving surgery. Axillary ultrasound is mandatory before surgery with predefined imaging criteria for inclusion. Ultrasound-guided core needle biopsy or needle aspiration of a suspicious node is allowed. Patients will be randomized (1:1) into the no-SLNB (test) and SLNB (control) groups. A total of 1734 patients are needed, considering a 5% non-inferiority margin, 5% significance level, 80% statistical power, and 10% dropout rate. All patients in the two groups will receive ipsilateral whole-breast radiation according to a predefined protocol. The primary endpoint of this trial is the 5-year invasive disease-free survival. The secondary endpoints are overall survival, distant metastasis-free survival, axillary recurrence rate, and quality of life of the patients.

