## Methods and design

### Study design

The NAUTILUS trial is a prospective multicenter randomized controlled trial. Ten tertiary care hospitals in South Korea are participating in this trial. Patients with invasive breast cancer who have tumors less than 5 cm and clinically negative axillary lymph nodes and are expected to undergo breast-conserving surgery (BCS) are randomized (1:1) to the SLNB and no-SLNB groups. Eligible patients undergo AUS for the assessment of lymph node status before enrollment. Core-needle biopsy or fine-needle aspiration of the node is performed if a patient has a suspicious lymph node based on AUS findings (Fig. 1). The patients are blinded to the randomization process until the surgery. The study is expected to last for 7 years, with 2 years for registration and 5 years for follow-up (Fig. 2). Patient recruitment was started on September 1, 2020, and the first patient was recruited on September 15, 2020. The enrolment is estimated to be completed in April 2022.

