### Sample size calculation

We designed the NAUTILUS study to determine whether the no-SLNB group was not inferior to the standard SLNB group. In the NSABP B-32 study, the 5-year DFS was 88.6% for cT1–2 N0 breast cancer [2]. We assumed that the DFS of our study patients would be lower than this because lymph node-positive patients will be included in our study. In the ACOSOG Z0011 study, the 5-year DFS was 83.9% for cT1–2 N1 (1 or 2 lymph node-positive) [6]. We assumed that the DFS of our study patients would be higher than this. As a result, the expected 5-year DFS of the control group of our study is 86%.

The 5% non-inferiority margin, 80% power, 5% two-sided significance level resulted in a sample size of 780 per study arm. Assuming a 10% dropout rate, 1734 patients need to be randomized. Patients are recruited competitively from each institution.

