### Interventions and follow up

Additional surgery involving the axilla after the results of SLNB are obtained in the control arm is dependent on the guideline of each treatment center. In both arms, adjuvant systemic therapy after surgery follows the guidelines of each center. Ipsilateral whole-breast radiation is mandatory for both arms. For the no-SLNB arm, the inclusion of axillary levels I and II within the tangential field or setting the upper margin of the field within 2 cm of the humeral head is recommended. The fractionation scheme follows 23–28 × 1.8–2.0 Gray (Gy) or 13–16 × 2.5–3.0 Gy. The boost to the tumor bed may be applied according to the policy of each center.

Follow-up of the patients will last for up to 5 years after surgery. The date of visit, status of disease progression, survival, adverse events, and quality of life findings will be reported at intervals of 3–6 months (according to each center’s policy). QoL questionnaires are acquired from the patients 1 and 2 years after the randomization using EORTC-BR23 and EORTC-QLQ-C30.

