### Statistics

For nominal variables such as self-reported complications in each arm/group, the total number of patients, percentile, and frequency will be presented and analyzed using the chi-squared test or Fisher’s exact test. Continuous variables, such as age and tumor size, will be summarized using descriptive statistics (mean, standard deviation, median, etc.), followed by analysis using Student’s t-test or the Mann-Whitney U-test as a non-parametric test.

The statistical significance of the 5-year DFS, which is the primary endpoint, overall survival, and distant DFS will be determined using Kaplan-Meier analysis and the log-rank test. Cox proportional hazard regression analysis will be used to assess the prognostic significance of variables. For every statistical analysis, a *p*-value of < 0.05 will be considered statistically significant.

An interim analysis for the primary endpoint is planned once, and an interim analysis is performed 5 years from the date of IRB approval, and a final analysis is performed after at least 224 events have occurred. Disease-independent death is defined as a competing event. Fine and Gray regression is performed to verify the statistical hypothesis for comparison between groups, and the significance level used for interim and final analysis is calculated based on the O’Brien Fleming α-spending function, and the analysis uses SAS 9.4 Proc seq test.

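### The final analysis waits for 224 events with no calendar alternative, while follow-up stops at 5 years per patient: at the planned 86% DFS the trigger has no reserve and may never be met

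*Protocol article*

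**What the plan says.** Four statements in the protocol article bear on the timing of the final analysis.

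- **Trigger** (Statistics): "a final analysis is performed after at least 224 events have occurred". No calendar date or fallback accompanies it. The one interim analysis does have a calendar date, and the significance levels come from an O'Brien-Fleming spending function.
- **Follow-up per patient** (Interventions and follow up): "Follow-up of the patients will last for up to 5 years after surgery".
- **Study duration** (Study design): "The study is expected to last for 7 years, with 2 years for registration and 5 years for follow-up".
- **Planning values** (Sample size calculation): "the expected 5-year DFS of the control group of our study is 86" per cent. The same section then derives the number per arm: "The 5% non-inferiority margin, 80% power, 5% two-sided significance level resulted in a sample size of 780 per study arm". After an allowance of 10% for loss, it arrives at a total of 1,734 to randomise.

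The 86% is placed between two published figures, 88.6% and 83.9%. The plan expects its own DFS to lie below the first and above the second.

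**The concern.** An event trigger works when follow-up stays open until the count is reached. Here follow-up appears to close patient by patient at 5 years. With a fixed number of patients and a fixed horizon, the number of events has a ceiling, and that ceiling should lie comfortably above the trigger. If it does not, the written rule can leave the trial with no defined final analysis.

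The sponsor would then have to extend follow-up unplanned, or choose a closing date once the events were known to fall short. If information is measured against 224 events, the spending function would also not reach its end by its own definition. For a confirmatory non-inferiority claim, both situations are better settled in advance.

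**Working it through.** **Inputs.** Trigger 224 (Statistics). 5-year DFS 86%, with 88.6% and 83.9% as the bracketing figures; 780 per arm, hence 2 × 780 = 1,560 evaluable; 10% dropout; 1,734 randomised (all from Sample size calculation). Allocation 1:1 (abstract, Methods). Follow-up of at most 5 years (Interventions and follow up). Assumptions made here: exponential event and dropout times, both arms at the same DFS, competing deaths ignored.

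**Step 1. Reproduce the plan's figures.** Randomised number: 780 / 0.9 = 867 per arm, and 2 × 867 = 1,734, exact.

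Trigger: the hazard ratio at the margin is ln(0.81)/ln(0.86) = 1.397, with log 0.3344. Schoenfeld's formula at one-sided 5% and 80% power gives 4 × (1.645 + 0.842)² / 0.3344² = 221.1, so 222. Freedman's gives 226. With O'Brien-Fleming-type spending and one look at an assumed 60% information, the requirement is 224.4. So 224 is reproduced as a log-hazard-ratio event count at one-sided 5%. At the two-sided 5% stated under Sample size calculation, the same formulas give 281 and 286.

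**Step 2. Expected events under a 5-year cap per patient, at 86%.**

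- Dropouts contribute no events: 1,560 × 0.14 = 218.4.
- Constant-hazard dropout of 10% over 5 years: event hazard λ = −ln(0.86)/5 = 0.03016 and dropout hazard δ = −ln(0.9)/5 = 0.02107. Events = 1,734 × λ/(λ+δ) × (1 − exp(−5(λ+δ))) = 1,734 × 0.1331 = 230.7.
- No loss at all: 1,734 × 0.14 = 242.8.

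**Step 3. Chance of ever reaching 224 (exact binomial), at 86%.**

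| Treatment of dropout | Expected events | Chance of at least 224 |
|---|---|---|
| Contribute none | 218 | 35% |
| Exponential 10% | 231 | 69% |
| No loss | 243 | 91% |

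**Step 4. Sensitivity to DFS, same cap.**

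| 5-year DFS | Contribute none | Exponential 10% | No loss |
|---|---|---|---|
| 88.6% | 178 | 188 | 198 |
| 86% | 218 | 231 | 243 |
| 83.9% | 251 | 265 | 279 |

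At 88.6% the chance of reaching 224 is at most 3% (no loss). At 83.9% the expected count exceeds 224 throughout. The DFS at which the expected count equals 224 is 85.6%, 86.4% and 87.1% for the three columns, so the planning value sits almost on the break-even. If the arms were at 86% and 81%, the expected count is 257 on 1,560 and 286 on 1,734.

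**Step 5. The other reading of follow-up.** If all patients were followed to a common close at year 7 after uniform 2-year entry, 86% gives 258 (1,560 patients) or 270 (1,734 with dropout), both above 224. At 88.6% the same reading gives 211 and 220, still short.

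**The case against.** **Which reading of follow-up is meant.** The strongest reply is that the shortfall depends on a per-patient cap. The 7-year duration under Study design could mean a common close, and then the trigger is met at 86%. This stands as a condition on the finding. The follow-up section does count its 5 years from surgery, which favours the cap, and the document does not settle the matter.

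**Attainability.** A reader might infer that 224 cannot be reached. The documents do not support that. At 86% the trigger lies inside the expected range, and the 218 is a pessimistic treatment, because Kaplan-Meier and Fine-Gray methods count events that occur before censoring. A worse DFS in either arm raises the count.

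**The planning value itself.** A reader might also infer that 86% is too low for patients selected as node-negative on ultrasound, so that the 88.6% row is the realistic one. The plan never states that 86% is a weighted mix of the two published figures, gives no node-positive share for its own patients, and expects DFS below 88.6%. That row is a sensitivity case only. Treating disease-independent death as a competing event could lower the count further, but the documents give no figure for it.

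**Consequences.** Setting a date from pooled event counts does not by itself inflate type I error, and a spending function can release all remaining alpha at a final look whatever the count. True, but the published rule does not say that such a look would take place.

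**Condensed article.** The full protocol or analysis plan may hold a calendar backstop. That limits confidence. The point rests on the rule that is printed, which conflicts with the printed follow-up, and not on an omitted detail.

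**Conclusion.** The point holds in a limited form. Read together, the event-only trigger and the 5-year cap per patient leave no reserve: about 218 to 231 events at the planned 86% under the planned dropout (243 with none), against 224 required. The trigger would go unmet with probability of about 31% to 65% under the planned dropout, or 9% with no loss.

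This rests on a per-patient cap, equal arms, exponential times and no allowance for competing deaths, which could only lower the count. Under a common close at year 7 the problem disappears at 86%. What is established is that the rule may fail to fire, not that it will.

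The match of 224 to a one-sided rather than a two-sided 5% level is a separate matter. The finding on timing does not depend on it.

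**What to change.** 1. Reconcile the Study design, Interventions and follow up, and Statistics sections on whether each patient's follow-up ends at 5 years or continues to a common close.
2. Add a calendar rule to the trigger, for example: *The final analysis is performed when every randomised patient has completed the 5-year visit, died or withdrawn, even if fewer than 224 events have occurred; all remaining alpha is spent at that analysis.*

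The test and the way information is measured can stay as they are. The cost is a wording change in the protocol and the analysis plan, with no added patients.

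The downside is some loss of power for the event-driven Fine-Gray comparison when events fall short, and the plan should restate it. As a guide, using the approximation from step 1 with the margin held at a hazard ratio of 1.397 and one-sided 5%, power is Φ(0.3344 × √D / 2 − 1.645). That gives 80.4% at D = 224, 79.5% at 218 and 72.1% at 178. At one-sided 2.5% (1.96 in place of 1.645), the corresponding values are 70.6%, 69.5% and 60.7%.

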### Study outcomes

The primary endpoint is the 5-year invasive DFS, and the secondary endpoints are OS, distant metastasis-free survival, axillary recurrence rate, local recurrence rate, and self-reported adverse events. In addition, QoL will be evaluated twice at 1 year and 2 years after surgery. An interim analysis will be conducted after a 3-year follow-up.

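### Two unreconciled analyses are named for the primary endpoint, and one of them (Fine-Gray with disease-independent death competing) does not test the disease-free survival on which the trial was sized

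*Protocol article*

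**What the plan says.** Study outcomes names the endpoint: "The primary endpoint is the 5-year invasive DFS". The article does not list its component events.

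Sample size calculation works from published DFS rates: "In the NSABP B-32 study, the 5-year DFS was 88.6% for cT1–2 N0 breast cancer" and "In the ACOSOG Z0011 study, the 5-year DFS was 83.9% for cT1–2 N1". It settles between them: "the expected 5-year DFS of the control group of our study is 86" (per cent). It then states "The 5% non-inferiority margin, 80% power, 5% two-sided significance level resulted in a sample size of 780 per study arm" and "Assuming a 10% dropout rate, 1734 patients need to be randomized". No hazard-ratio margin appears anywhere.

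Statistics gives two analyses. In one paragraph, the significance of 5-year DFS, "which is the primary endpoint, overall survival, and distant DFS will be determined using Kaplan-Meier analysis and the log-rank test". In the next, which opens with the interim analysis of the primary endpoint, "Disease-independent death is defined as a competing event. Fine and Gray regression is performed to verify the statistical hypothesis for comparison between groups". The same sentence bases the interim and final significance levels on O'Brien-Fleming alpha spending. The paragraph sets the final analysis at no fewer than 224 events, without saying whether disease-independent deaths count towards them.

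**The concern.** Both analyses are attached to the primary endpoint, and nothing says which decides. They also estimate different things. In a Kaplan-Meier or log-rank analysis of DFS as usually understood, a death without recurrence is a failure, so no death is left to compete. If disease-independent death is a competing event, it is not a failure, and Fine-Gray compares the cumulative incidence of disease events only.

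One of two statements must therefore give way. If such deaths are events, they cannot also be competing. If they are not events, the endpoint is not DFS in the usual sense, and the 86% rate and 5% margin were taken from a different quantity.

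At stake is the trial's main conclusion. The two analyses could disagree, and what counts as non-inferior would shift with a death rate that was never specified. The Fine-Gray version also needs each death classed as disease-related or not. Counting deaths from any cause removes that judgement from the primary result.

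**Working it through.** **Inputs from the article.** Control 5-year DFS 86% (event risk 14%); margin 5%, read as percentage points; 80% power; two-sided 5%, so one-sided 2.5%; 780 per arm (1,560 in total); 10% dropout; 1,734 randomized; 224 events.

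**Input not in the article.** The 5-year share of disease-independent deaths, x. Assumed range: 1 to 4 of the 14 percentage points.

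**Step 1: the stated size.** For a non-inferiority comparison of two proportions, n = 2 × 0.86 × 0.14 × (1.960 + 0.842)² / 0.05² ≈ 757 per arm, against 780 stated (within 3%). For dropout, 1,560 / 0.90 = 1,733.3, rounded up to 1,734, which is exact. The size follows from the full 14% DFS failure risk, with no allowance for a competing event.

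**Step 2: the margin as a hazard ratio for DFS.** ln(0.81) / ln(0.86) = 1.397. Schoenfeld's formula, 4 × (z_α + z_β)² / (ln 1.397)², gives 222 events at one-sided 5% and 281 at two-sided 5%. So 224 is close to the one-sided 5% count for the full DFS endpoint. That this differs from the stated two-sided level is a separate matter.

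**Step 3: with disease-independent death competing.** The control cumulative incidence of disease events becomes F = 0.14 − x.
- Carrying over 5 points, the tolerated subdistribution HR is ln(1 − F − 0.05) / ln(1 − F).
- Carrying over HR 1.397, the tolerated absolute difference is 1 − (1 − F)^1.397 − F.
- Expected 5-year disease events, with equal arms, are 1,560 × F. With all 1,734 patients and no dropout, they are 1,734 × F.

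| x (points) | F | HR equal to 5 points | Points equal to HR 1.397 | Events, 1,560 | Events, 1,734 |
|---|---|---|---|---|---|
| 0 | 14% | 1.397 | 5.0 | 218 | 243 |
| 1 | 13% | 1.425 | 4.7 | 203 | 225 |
| 2 | 12% | 1.458 | 4.4 | 187 | 208 |
| 3 | 11% | 1.496 | 4.0 | 172 | 191 |
| 4 | 10% | 1.543 | 3.7 | 156 | 173 |

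**Step 4: the event trigger.** Interventions and follow up limits follow-up to 5 years after surgery. On that basis, from x = 2 upwards the expected disease events stay below 224 even if all 1,734 patients are followed without dropout. With all deaths counted, the expectation is 218 to 243, which straddles 224. What counts as an event therefore bears on whether and when the final analysis is triggered.

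**The case against.** The article is a condensed report. It does not list the components of invasive DFS, and such a list commonly sits in the full protocol. The mismatch of endpoints therefore rests on the ordinary meaning of DFS. That limit stands, but the two analyses are both stated in the article, so their conflict is not a matter of omitted detail.

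The share of disease-independent deaths is also an assumption. Four of 14 points would be 29% of all events, and the Discussion describes a younger, more premenopausal population, which points to the low end. At 1 point the hazard-ratio shift is only from 1.40 to 1.43. This stands too.

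Several stronger readings are tempting but not supported:

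- **That the Fine-Gray analysis loosens the margin.** It does so only on the relative scale, and only if 5 points is carried over. If HR 1.397 is carried over, the absolute margin tightens. On the absolute scale, 5 points remains 5 points. Counting unrelated deaths equally in both arms pulls a composite hazard ratio towards 1, so the competing-risk version is not inherently the permissive one.
- **That fewer events mean lost power.** With a 5-point margin on the cumulative-incidence difference, power at 780 per arm rises from 81% at x = 0 to 84–91% for x = 1 to 4. Power falls only if HR 1.397 is kept: 222 events would still be needed at one-sided 5%, with 203–156 expected.
- **That 224 events cannot be reached.** If follow-up ran to the end of the 7-year study, constant-hazard DFS would give an average event risk of 16.5%, or about 258 events in 1,560 patients.
- **That Fine-Gray is the sole confirmatory test.** Log-rank is also named for the primary endpoint.
- **That cause-of-death classification will be biased.** Patients are masked only until surgery, but the article does not say who classifies deaths or whether they are masked.
- **That DFS and invasive DFS are two endpoints.** The Statistics section calls 5-year DFS the primary endpoint, which reads as shorthand.

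**Conclusion.** The point holds. The article attaches two analyses with different estimands to one primary endpoint, ties the alpha spending to the one that does not match the sizing, and gives no rule for which decides. The conclusion assumes that DFS has its usual meaning. If the full protocol excludes disease-independent deaths from invasive DFS, the endpoint's name and the DFS-based sizing need correcting instead, so the passages must be reconciled either way.

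The size of the shift is conditional. For an assumed 1 to 4 points of disease-independent death, the same 5-point margin is a subdistribution HR of 1.43 to 1.54 rather than 1.40, while a fixed HR of 1.40 is a margin of 4.7 to 3.7 points. The direction depends on a scale that the article does not fix. The firm conclusion is that the criterion is not fully determined, not that it is looser or that the trial is underpowered.

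**What to change.** 1. Define the primary endpoint once, as invasive DFS with death from any cause as an event, and use that name in Sample size calculation, Study outcomes and Statistics.
2. Name one deciding non-inferiority analysis and state the 5-point margin on its scale. Examples are the confidence limit for the difference in 5-year Kaplan-Meier estimates against −5 points, or a Cox hazard ratio against 1.40, the equivalent under proportional hazards at 86%.
3. State that the 224 events count this endpoint, and apply the O'Brien-Fleming spending to this analysis.
4. Keep Fine-Gray and cumulative incidence for axillary and local recurrence, where death does compete, and as a supportive analysis of disease events.

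No new data are needed. The cost is a change of wording, plus aligning the event trigger and the alpha-spending boundary to the chosen test. That alignment is more work for a Kaplan-Meier difference, because 224 events corresponds to a hazard-ratio calculation.

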## Discussion

The primary aim of the NAUTILUS study is to demonstrate the oncologic safety of omitting axillary surgery for selected lymph node-negative early breast cancer patients undergoing BCS and whole breast irradiation. The standard procedure for axillary surgery for these patients includes SLNB. Studies have reported that the 5-year axillary recurrence rate of patients with negative nodes detected by SLNB is 0.3–1.6% [5, 9–11]. The overall 8-year survival and 5-year DFS rates in the NSABP B-32 trial were reported to be 90.3 and 88.6%, respectively [2]. Considering that the FNR of the SLNB amounts to 5–10% and the SLNB does not completely get rid of metastatic lymph nodes, the aforementioned prognosis indicates that the unremoved metastasized lymph nodes do not lead to clinical recurrence in most cases. The very low axillary recurrence rate in the Z0011 trial also supports the hypothesis [6].

The morbidity rate after SLNB is generally lower than that after ALND; however, SLNB also has significant residual morbidity. In the NSABP B-32 study, arm volume differences of ≥10% at 36 months were evident for 8% of the SLNB group, and numbness and tingling peaked at 6 months for 15 and 10% of the SLNB group [12]. Kozak et al. reported undesirable sequelae, such as limited mobility in the shoulder joint, gradual increase in limb circumference, and pain, in patients after SLNB [13]. Based on the findings of other studies, lymphedema was reported in 7.5–9.0% of patients after SLNB after 6 months of follow-up and 5.2% even after 5 years of follow-up [12, 14–16]. Shoulder abduction deficit and sensory changes, such as numbness, pain, and paresthesia, have also been reported in patients after SLNB [12, 16, 17]. These morbidities are known to have physical, psychological, and emotional impact on the quality of life [18].

Eliminating or de-escalating axillary surgery aligns with the contemporary treatment trends. At least three clinical trials are being carried out, including the SOUND, INSEMA, and BOOG 2013–08 trials. The SOUND trial was designed to assess the non-inferiority of the 5-year distant DFS of cT1N0 breast cancer patients after SLNB to that after observation [19]. The INSEMA trial randomized cT1–2 N0 breast cancer patients into 4 groups, including the SLNB and SLNB-omission groups, and planned to analyze the 5-year DFS [20]. The BOOG 2013–08 trial also randomized cT1–2 N0 breast cancer patients into two groups, namely, the SLNB and no-SLNB groups, and evaluated the non-inferiority of regional recurrence in the no-SLNB group after 5- and 10-year follow-up [21]. These trials and our NAUTILUS trial altogether will answer the very important question that can alter the axillary surgery practice in breast cancer.

There are differences between this study and the aforementioned ongoing studies; however, this study has advantages. NAUTILUS is the only study targeting Asian breast cancer patients who are younger and more premenopausal than western women in terms of epidemiologic difference. Second, we have detailed ultrasonographic criteria for selecting patients and that is shared with breast radiologists (imaging) in each participating institution. Third, NAUTILUS aims to analyze the quality of life of each arm, which will add evidence to justify skipping SLNB. Cost-effectiveness will also be assessed for each arm.

In summary, the NAUTILUS trial aims to determine whether SLNB can be skipped for a specific breast cancer patient group. If there is no significant difference between the two randomized arms, patients who meet the criteria can have increased quality of life with less surgical morbidity and decreased medical costs but equivalent oncologic outcomes by avoiding unnecessary surgical procedures.

